### Sample size

Sample size was estimated as described previously [19], which considered a change in the population mean on the numerical rating scale (NRS) for each group (1, EM group; 2, TIM group; 3, usual care group). The null and alternative hypotheses are:$$ {H}_{01}:{\mu}_1-{\mu}_2=0,\kern0.5em {H}_{02}:{\mu}_1-{\mu}_3=0 $$$$ {H}_{11}:{\mu}_1-{\mu}_2\ne 0,\kern0.5em {H}_{12}:{\mu}_1-{\mu}_3\ne 0 $$

H01 : the first null hypothesis

H02 : the second null hypothesis

H11 : the first alternative hypothesis

H12 : the second alternative hypothesis

μ1, μ2, μ3 : the true mean change of pain on the NRS before and after treatment (1: EM, 2: TIM, 3 : usual care)

We assumed that the true mean differences in pain on the NRS before and after treatment with EM and TIM were 12.25 (standard deviation (SD) 18.52) and 1.4 (SD 16.27), respectively. Thus, we calculated the sample size needed to achieve 80% power at a significance level of 0.05 using the following equation:$$ n=\frac{\left({\sigma}_1^2+{\sigma}_2^2\right){\left({Z}_5+{Z}_{\upbeta}\right)}^2}{{\left({\mu}_1-{\mu}_2\right)}^2}\approx 41 $$

σ1, σ2 : the true standard deviation (1 : EM, 2 : TIM)

α : significance level

β : power

Z : points on normal distribution to give required power and significance

The mean difference between the usual care group and the EM and TIM groups is expected to be larger than that between the EM and TIM groups. Thus, sample size was estimated larger because of using the mean difference between the EM and TIM groups.

Thus, the estimated sample size was 41 participants per group. Considering an anticipated dropout rate of 10%, we plan to include a total of 138 participants, with 69 participants per institution.

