### Statistical analysis

An independent statistician blinded to group allocation will perform statistical analysis on the full analysis set (FAS) and will also perform a pre-protocol (PP) analysis. Missing data will be replaced according to the principle of the last observation carried forward (LOCF) method.

Demographic and other baseline values will be analyzed using descriptive statistics for each group. For comparison of characteristics among the three groups, continuous data will be expressed as mean and SD and analyzed using analysis of variance (ANOVA) or the Kruskal-Wallis test. Categorical data will be presented as frequency and percentage and analyzed using chi-squared test or Fisher’s exact test.

The primary endpoint is the mean change in pain on the NRS from week 1 to week 6. To test the significance of changes in pain on the NRS between groups, we formulated two sets of hypotheses.

The first null hypothesis (H_01_) is that the EM and TIM groups have no difference in the true mean change of pain on the NRS before and after treatment. The first alternative hypothesis (H_11_) is that the EM and TIM groups have a difference in the true mean change in pain identified on the NRS before and after treatment.

The second null hypothesis (H_02_) is that the EM and usual care groups have no difference in the true mean change in pain on the NRS before and after treatment. The second alternative hypothesis (H_12_) is that the EM and usual care groups have a difference in the true mean change in pain on the NRS before and after treatment.

ANOVA or the Kruskal-Wallis test will be used to determine the significance of differences in the measured values before and after treatment in each group. To compare the three groups, analysis of covariance (ANCOVA) will be performed for the primary endpoint, with a fixed effect for the treatment group. Baseline pain on the NRS, age, Kellgren-Lawrence grade, and duration of KOA symptoms will be considered as covariates in this analysis. A *p* value below 0.05 will be considered significant for all analyses, and 95% confidence intervals (CIs) will be calculated.

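### Two primary hypotheses share a blanket 0.05 threshold with no rule linking them; if they are tested separately and either counts, the two-sided family-wise error is about 9% when both nulls are true

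*Protocol article*

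**What the plan says.** Under Statistical analysis, the protocol article says of the primary endpoint that "we formulated two sets of hypotheses". The first alternative "is that the EM and TIM groups have a difference in the true mean change in pain identified on the NRS before and after treatment". For usual care, the other alternative "is that the EM and usual care groups have a difference in the true mean change in pain on the NRS before and after treatment". Both are two-sided, and Sample size states the same pair in symbols as H01/H11 and H02/H12.

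The model comes next: "To compare the three groups, analysis of covariance (ANCOVA) will be performed for the primary endpoint, with a fixed effect for the treatment group". Baseline NRS pain, age, Kellgren-Lawrence grade and symptom duration are listed as covariates. The section then sets one threshold, a p "value below 0.05 will be considered significant for all analyses", and promises 95% confidence intervals.

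Under Sample size, "we calculated the sample size needed to achieve 80% power at a significance level of 0.05" is applied to EM against TIM alone. The difference from usual care is expected to be larger and is not sized separately.

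Neither section gives an order of testing, a division of alpha, an adjustment, an overall test as a precondition, or a statement on whether one rejection is enough or both are needed.

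**The concern.** The two nulls feed one conclusion about EM. Objective gives a single aim, the efficacy and safety of EM relative to both comparators, and Discussion reduces it to whether EM works and is safe in practice. With two routes to a positive primary result, each at the full 0.05, the chance that at least one opens by luck exceeds 0.05 unless a rule ties them together.

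The decision test is also left open. A three-group ANCOVA yields a treatment test with 2 degrees of freedom and also yields each pairwise contrast. The text does not say which of these decides H01 and H02. The overall test does not identify the pair or the direction behind a significant result.

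At stake is the error rate attached to the primary claim. It depends on a rule that the article does not fix and that could therefore be settled after the data are seen.

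**Working it through.** **Inputs.** From Sample size: mean changes 12.25 (EM) and 1.4 (TIM), SDs 18.52 and 16.27, power 80%, alpha 0.05, 41 per group, 10% dropout, 138 in total. From Randomization and blinding: 1:1:1 allocation. From Statistical analysis: two two-sided primary nulls and 0.05 throughout.

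**1. Reproducing the plan's sample size.**
- Formula: n = (σ₁² + σ₂²)(z_α + z_β)² / (μ₁ − μ₂)².
- σ₁² + σ₂² = 342.99 + 264.71 = 607.70; (12.25 − 1.4)² = 10.85² = 117.72.
- Two-sided 0.05: 607.70 × (1.960 + 0.842)² / 117.72 = 40.52, rounded up to 41.
- One-sided 0.05: 31.9, i.e. 32, which does not match.
- Dropout: 41 / 0.9 = 45.6, so 46 per group and 3 × 46 = 138.

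The stated numbers reproduce, and only with the whole two-sided 0.05 spent on EM against TIM.

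**2. Correlation of the two contrasts.** Both contain the EM mean. With equal arms and equal variances the covariance is σ²/n and each variance is 2σ²/n, so ρ = 0.5. With SD 18.52 in EM and 16.27 assumed in both other arms, ρ = 342.99 / 607.70 = 0.56.

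**3. Family-wise error, both nulls true, each contrast tested separately at two-sided 0.05.** The error is 1 − P(|Z₁| ≤ 1.96 and |Z₂| ≤ 1.96), with Z₁ and Z₂ bivariate normal.

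| Assumption | P(at least one false rejection) |
|---|---|
| ρ = 0.5 | 0.0907 |
| ρ = 0.56 | 0.0888 |
| Independent: 1 − 0.95² | 0.0975 |
| Upper bound: 0.05 + 0.05 | 0.10 |

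Simulation of 400,000 three-arm trials with t tests gave 0.0897 at 41 per group and 0.0908 at 46.

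**4. The same setting under other rules or definitions (simulated, 41 and 46 per group).**
- Only a false claim that EM is better counts: 0.0451 and 0.0453.
- A significant three-group F test is required first: 0.0410 and 0.0419.
- Both nulls must be rejected: 0.0094 at either size.

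If EM truly differs from usual care, as the plan expects, H01 is the only null that can be falsely rejected, and the error is 0.05.

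**5. Effect of splitting alpha (0.025 each).**
- n = 607.70 × (2.241 + 0.842)² / 117.72 = 49.07, so 50 per group. 50 / 0.9 = 55.6, so 56 per group and 168 in total.
- Power for EM against TIM with 41 per group: standard error √(607.70 / 41) = 3.850, and 10.85 / 3.850 = 2.818. Φ(2.818 − 1.960) = 0.805 at alpha 0.05; Φ(2.818 − 2.241) = 0.718 at 0.025. With all 46 analysed at 0.025 it is 0.771.

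**6. Effect of a fixed sequence, H02 then H01, each at 0.05.** H01 is claimed only if both contrasts are significant. The article gives no usual care figures, so I assume SD 16.27 (ρ = 0.56) and vary the EM minus usual care difference. The probabilities are bivariate normal, with means equal to each difference divided by the standard error (3.850 at 41 per group, 3.635 at 46).

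| EM minus usual care (assumed) | P(claim H01), n = 41 | P(claim H01), n = 46 |
|---|---|---|
| 10.85 (no larger than EM minus TIM) | 0.701 | 0.760 |
| 12.25 (no change on usual care) | 0.754 | 0.809 |
| 15 | 0.797 | 0.843 |
| Tested alone, no sequence | 0.805 | 0.847 |

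The sequence keeps N at 138. It costs little power for H01 when the usual care difference is clearly larger, and more when it is not.

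**The case against.** **The 9% rests on a sequence that the article does not state.** This is correct. If only the three-group test were run, its error would be 5%. If it were required before pairwise tests, the error would stay within 5%. The 9% belongs to separate contrasts with either one sufficient. The text states neither that rule nor any alternative, so the figure must carry its condition.

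**A reader might infer that the named ANCOVA tests neither hypothesis.** The documents do not support that. The sentence specifies a model, and that model yields both EM contrasts. The hypotheses, which name specific pairs, are set out just before it. Likewise, TIM against usual care is not a hypothesis of the trial, and nothing says that a difference there would be reported as EM efficacy. What stands is narrower: the contrasts are not named as the primary tests, and an overall effect alone does not locate a difference.

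**The two questions differ, and joint control is debatable.** One compares two active techniques; the other asks whether EM improves on usual care. That is a fair argument for separate error rates, but the article does not make it, and its single aim draws on both comparisons.

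**Multiplicity is commonly left to an analysis plan, and 0.05 could apply to adjusted p values.** A condensed article need not print the procedure. However, this one fixes a threshold for every analysis and sizes the trial with the full 0.05 on one contrast. A later split of alpha would leave EM against TIM below its stated power.

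**Conclusion.** The concern holds in conditional form. Two primary two-sided nulls share the EM arm, every analysis is judged at 0.05, and nothing links the two tests. The two-sided family-wise error is about 9% (0.089 to 0.0975 over the correlations tried, never above 0.10) if three things hold: the contrasts are tested separately, either rejection counts, and both nulls are true.

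A reader might take 9% as the trial's actual false-positive rate. The article does not support that, because the figure falls to 4.5% for a false claim that EM is better, to about 4% with a required overall test, and to 5% if EM truly differs from usual care. The defect is that the rule is open. It is worth closing because it governs the primary claim and, under Trial status, recruitment was still in progress.

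**What to change.** Name the adjusted-mean contrasts EM minus usual care and EM minus TIM, both from the single ANCOVA, as the tests of H02 and H01. Then fix one error-control rule that keeps 138 participants. For example: test H02 first at two-sided 0.05, and test H01 at two-sided 0.05 only if H02 is rejected. Starting with H02 follows the plan's own expectation that the usual care difference is the larger. A three-group test stated as a required first step would also hold the error at 5%. State that the overall test (unless adopted as that first step), TIM against usual care, the secondary outcomes and the subgroups are supportive only.

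The change is two or three sentences and no more patients. The downside is that H01, the comparison that sized the trial, cannot be claimed if H02 fails. Its chance of being claimed therefore falls somewhat below its stand-alone power, by an amount that depends on the true usual care difference, as the last table shows. Splitting alpha avoids that dependence but needs 168 participants to keep 80% power for EM against TIM.

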### Adverse events

Adverse events known to follow moxibustion treatment include blisters, redness, itching, burns, and respiratory symptoms. In every visit, adverse events will be reported by participants and examined by the practitioner. The presence of symptoms and their onset, duration, severity, and relationship with adverse events from treatment will be carefully recorded in the CRFs. To avoid potential adverse events, a treatment will be delayed by 3 days if the practitioner considers the participant unsuitable for moxibustion treatment, or if the participant indicates moderate fatigue or abnormal health. Vital signs will also be measured at every visit.

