**Methods:**

This is a multicenter, randomized, open, assessor-blinded, parallel-group clinical trial. A total of 138 eligible participants with KOA will be randomly allocated into three groups (electrical moxibustion, traditional indirect moxibustion, or usual care) with a 1:1:1 ratio. Participants in each moxibustion group will receive 12 sessions of moxibustion treatment at 6 acupoints (ST36, ST35, ST34, SP9, EX-LE4, SP10) plus up to 2 points of “ashi”, if needed, over a period of 6 weeks (2 sessions per week). A specifically designed device that provides thermal stimulation using electrical energy will be used for the electrical moxibustion group. Participants in the usual care group will receive usual treatment and self-care. The primary outcome measure is change in pain on a numerical rating scale (NRS) from week 1 to week 6. The secondary outcome measures are pain assessed on a visual analog scale (VAS), the Korean version of the Western Ontario and McMaster osteoarthritis index (K-WOMAC), patient global assessment (PGA), and the European quality of life five dimension five level scale (EQ-5D-5 L). Safety will be assessed by monitoring adverse events at each visit. Follow-up measurements will be performed at 12 weeks after baseline measurements.

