## Methods/design

### Objective

The aim of this trial is to assess the efficacy and safety of EM compared with TIM and usual care in patients with KOA.

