### Design and setting

This is a multicenter, randomized, open, assessor-blinded, parallel-group clinical trial. Eligible participants who meet the clinical criteria for KOA of the American College of Rheumatology (ACR) [18] will be enrolled. Two clinical research centers in Korea will participate: Dongguk University Bundang Oriental Hospital and Dongguk University Ilsan Oriental Hospital. A total of 138 participants with KOA will be randomly assigned to one of three groups (EM, TIM, or usual care) with a 1:1:1 ratio.

The study period is 12 weeks, and consists of a 6-week treatment phase and a 6-week follow-up phase. After randomization, participants in the EM and TIM groups will receive 12 sessions of treatment over 6 weeks. Participants in the usual care group will be assessed at 1, 4, and 6 weeks after baseline. Follow-up assessment by telephone will be conducted at 6 weeks after the end of treatment for all groups. Figure 1 outlines the trial procedures and Fig. 2 shows the schedules for enrollment, intervention, and assessments. The SPIRIT checklist is provided in Additional file 1.

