### Outcome assessments

#### Primary outcome

The primary outcome measure will be the mean change in pain on the NRS from week 1 (before treatment) to week 6. Participants in the EM and TIM groups will be asked to indicate a number between 0 and 100 that best describes the intensity of pain every week and at week 12 (follow-up check): 0 usually represents “no pain at all”, whereas 100 represents “the worst pain imaginable” [21]. Participants in the usual care group will be assessed using the same method at weeks 1, 4, 6, and 12.

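### Adverse events are sought at 12 sessions in each moxibustion arm but at only two or three usual-care visits, so the safety comparison with usual care is open to detection bias against moxibustion

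*Protocol article*

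**What the plan says.** The Objective section of the protocol article names both comparators for safety as well as efficacy: "The aim of this trial is to assess the efficacy and safety of EM compared with TIM and usual care in patients with KOA".

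The ascertainment rule appears twice. The abstract says "Safety will be assessed by monitoring adverse events at each visit". The Adverse events section says "In every visit, adverse events will be reported by participants and examined by the practitioner", and adds that onset, duration and severity go into the case report form.

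The visit schedules differ by arm. Under Design and setting, "participants in the EM and TIM groups will receive 12 sessions of treatment over 6 weeks", whereas "Participants in the usual care group will be assessed at 1, 4, and 6 weeks after baseline". The Primary outcome section gives the usual-care schedule again: "Participants in the usual care group will be assessed using the same method at weeks 1, 4, 6, and 12". That section also describes the primary change as running "from week 1 (before treatment) to week 6", which makes week 1 the baseline visit, while Design and setting places week 1 after baseline. All arms share one later contact: "Follow-up assessment by telephone will be conducted at 6 weeks after the end of treatment for all groups".

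**The concern.** A visit-based rule gives equal ascertainment only if the arms have equal visits, and here they do not. A moxibustion participant is asked and examined roughly twice a week. A usual-care participant may go two to four weeks between contacts. An event that could happen in any arm and soon passes, such as itching, a headache or a mild respiratory symptom, has more chances of being recorded under moxibustion. The examiner is the practitioner, a term the article uses for the person giving moxibustion. Usual care has no trial sessions, so it is unclear who fills that role there.

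At stake is one part of the stated aim. An excess of minor events with EM over usual care could reflect harm, more frequent asking, or both, and the plan as written gives no means of telling them apart. The Discussion lists lack of blinding and the absence of a sham as limitations, but not this.

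**Working it through.** **Visit counts, from the article.** EM and TIM: 2 sessions per week × 6 weeks = 12, which agrees with the stated 12. Usual care, treatment phase: weeks 1, 4 and 6 = 3 visits if week 1 is post-baseline, or weeks 4 and 6 = 2 visits if week 1 is baseline.

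- Treatment phase: 12/3 = 4.0 or 12/2 = 6.0.
- If the week-12 call also elicits events: 13/4 = 3.25 or 13/3 = 4.3.

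These ratios count opportunities. They do not measure the bias, because a participant asked after a longer gap may have more to report.

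**Illustrative size.** The article gives neither event rates nor a recall period, so the following are assumptions:

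- true event rates are equal in all arms and events are spread evenly over 42 days;
- a minor event is recorded only if a visit falls within w days after it;
- moxibustion visits are every 3.5 days, the last on day 42.

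The share of the 42 days covered is the sum, over visits, of the smaller of w and the gap since the previous visit, divided by 42. The gaps are 3.5 days (12 times) for moxibustion; 7, 21 and 14 days for usual care with three visits (days 7, 28, 42); and 28 and 14 days with two visits (days 28, 42). The apparent rate ratio is moxibustion coverage divided by usual-care coverage.

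| Window w | EM or TIM | Usual care, 3 visits | Usual care, 2 visits | Apparent ratio |
|---|---|---|---|---|
| 3.5 days | 42/42 = 100% | 10.5/42 = 25% | 7/42 = 17% | 4.0 to 6.0 |
| 7 days | 100% | 21/42 = 50% | 14/42 = 33% | 2.0 to 3.0 |
| 14 days | 100% | 35/42 = 83% | 28/42 = 67% | 1.2 to 1.5 |
| 21 days | 100% | 42/42 = 100% | 35/42 = 83% | 1.0 to 1.2 |
| 28 days | 100% | 100% | 42/42 = 100% | 1.0 |

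The distortion is large for events forgotten or healed within a week, modest at two weeks, and gone once recall spans the longest gap between usual-care visits. EM and TIM have the same schedule, so their ratio is 1 throughout. No sample-size figure is involved.

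**The case against.** **Recall may be long.** The case report form records onset and duration, which implies taking a history of events between visits, so the shortest windows are the less natural reading. This stands, and the upper end of the range should not be taken as the expected bias. It does not show that recall is complete over gaps of up to 21 or 28 days, and no diary, interim call or common look-back period is described.

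**No between-arm adverse-event test is stated.** The hypotheses concern pain, and tabulation and form wording may sit in documents not shown. It is therefore tempting but unsupported to quote a false-positive rate for such a test. A descriptive comparison carries the same bias, however, and the imbalance comes from a visit schedule and a collection rule that the article does state. The schedule figure (Fig. 2) was not available for this check; additional usual-care event checks shown there would change the count.

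**The bias runs one way.** A reader might infer that the EM versus usual care safety comparison cannot be interpreted at all. The article does not support that. More looking can only add recorded events under moxibustion, so a finding of no excess with EM would still be informative. Serious or lasting events would probably surface at any visit, and treatment-site burns and blisters cannot arise from usual care.

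**Asking everyone could unblind the assessor.** The article relies on a blinded assessor, and hearing of burns or blisters at week 4 could reveal allocation before the week-6 primary pain rating. This stands, and it determines who should ask the question and when.

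**Conclusion.** The concern holds in a limited form. The stated rules give 12 ascertainment points against two or three during treatment, in a comparison the Objective itself names. The direction, more events recorded under moxibustion, follows from the schedule. The size does not: the apparent ratio runs from about 4 to 6 down to 1 according to the assumed recall window, and assumes equal true rates. The bias bears mainly on transient, non-specific events and on overall event rates for EM or TIM against usual care. EM versus TIM is unaffected.

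A reader might also infer that only perfect recall would remove the bias. Under this model that is not so: recall over the longest usual-care gap (21 days with three visits, 28 with two) is enough.

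**What to change.** At the contacts all arms already share (weeks 4 and 6 and the week-12 call), put one identical structured adverse-event question to every participant, covering the period since the last common contact. Existing site staff other than the blinded outcome assessor should ask it, after that contact's outcome measures are complete. Base the comparative adverse-event statement for EM or TIM against usual care on those answers. Keep the every-visit record, report all its events descriptively by arm, and use it for EM versus TIM. State whether week 1 is baseline, so that the number of usual-care visits is clear.

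The cost is one case report form item and one extra table, with no added visits. Brief events seen only at sessions do not enter the like-for-like comparison, though they are still reported. Repeated questioning at sessions may prime moxibustion participants to report more, so the bias is reduced and not removed. Recruitment is under way according to Trial status, so the change reaches only remaining participants, and the unequal ascertainment should also be stated as a limitation.
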